#### 8.4.2. Identification of Adverse Events and Serious Adverse Events

When identifying AEs and SAEs, care shall be taken to avoid bias, for example by asking open-ended questions to the subject regarding the occurrence of events.

#### 8.4.3. Follow-up of Adverse Events and Serious Adverse Events

After the initial AE/SAE report, the principal investigator or sub-investigator shall actively follow each subject at subsequent visits or contacts. All AEs shall be followed until the event resolves, the condition stabilizes, it becomes evident that the event was caused by another factor, or the subject becomes lost to follow-up (as defined in 7.3). Details of the follow-up procedures are provided in Appendix 2-10.2.3.

#### 8.4.4. Regulatory Reporting Requirements for Serious Adverse Events

The principal investigator or sub-investigator shall, in order to fulfill their legal obligations and

ethical responsibilities for subject safety and the safety of the trial intervention, promptly initiate the reporting process for an SAE in accordance with Appendix 2-10.2.4 and the "Procedures for Handling Safety Information." In addition, the trial coordinator shall, in accordance with Appendix 2-10.2.4 and the "Procedures for Handling Safety Information," make reports to the Pharmaceuticals and Medical Devices Agency as required to satisfy regulatory obligations.

#### 8.4.5. Pregnancy Information

Details of all pregnancies occurring in women of child-bearing potential shall be tracked from the time of investigational product administration until the end of the observation period in accordance with the following procedures.

- ✓ If a pregnancy is reported, the principal investigator shall record the pregnancy information on the appropriate form and submit it promptly to the trial coordinator upon becoming aware of the subject's pregnancy.
- ✓ Pregnancy itself is not considered an AE or SAE; however, pregnancy complications or elective termination shall be reported as an AE or SAE.
- ✓ If the outcome of the pregnancy is abnormal (e.g., spontaneous abortion, fetal death, stillbirth, congenital anomaly, ectopic pregnancy), it shall be reported as an SAE.
- ✓ The subject shall be followed to ascertain the pregnancy outcome. The principal investigator or sub-investigator shall collect follow-up information concerning the subject and the neonate and report it to the trial coordinator.
- ✓ The principal investigator or sub-investigator shall, if an SAE related to pregnancy occurs after trial completion and a reasonable possibility of a causal relationship with the investigational product is judged, report it to the trial coordinator in accordance with this section. The principal investigator and sub-investigator are not obligated to actively collect such information after a subject has discontinued trial participation, although they may become aware of an SAE through spontaneous reporting.
- ✓ Evaluation of the disease condition for participants who become pregnant during the trial may be continued if the principal investigator or sub-investigator deems it appropriate.

#### 8.4.6. Cardiovascular Events and Deaths

No cardiovascular events of particular concern are anticipated in this trial.

#### 8.4.7. Disease-Related Events

Events that may occur in association with the underlying disease or the surgical procedure include pre-retinal hemorrhage, intraretinal hemorrhage, sub-retinal hemorrhage, vitreous hemorrhage, serous retinal detachment, macular edema, re-bleeding, hard exudates, etc. These

events shall be evaluated, in light of the subject's underlying disease condition, for the anticipated intensity, frequency, duration, and any reasonable possibility of association with the trial intervention, to determine their relevance as an AE or SAE and to assess causality with the investigational product.

#### 8.5. Pharmacokinetics (PK)

Pharmacokinetic assessments will not be performed in this trial.

#### 8.6. Pharmacodynamics

Pharmacodynamic assessments will not be performed in this trial.

#### 8.7. Genetics

Genetic assessments will not be performed in this trial.

#### 8.8. Biomarkers

Biomarker assessments will not be performed in this trial.

#### 8.9. Immunogenicity Assessment

Immunogenicity assessments will not be performed in this trial.

#### 8.10. Utilization of Medical Resources and Health Economics

Health-economic analyses, utilization of medical resources, and health-economic parameters will not be evaluated in this trial.

### 9. Statistical Considerations

The statistical analysis plan will be finalized prior to database lock and will contain a more technical and detailed description of the statistical analyses described in this section. This section provides a summary of the planned statistical analyses for the most important endpoints, including primary and secondary endpoints.

#### 9.1. General Considerations

##### ● Baseline Definition

Baseline assessments or events are defined as assessments or events that occurred prior to the date and time of administration of the investigational product. When multiple valid assessments or events are available, the assessment closest to the investigational product administration date (and time, if collected) shall be used as the baseline for analysis.

- Summary Statistics

For continuous variables, summary statistics shall include the number of observations, mean, standard deviation, minimum, median, maximum, first quartile (25th percentile), and third quartile (75th percentile). For categorical variables, summary statistics shall include the number of observations and the frequency and percentage (%) of each category.

Means, standard deviations, medians, first quartiles, and third quartiles shall be rounded to two decimal places and displayed to one decimal place. Minimum and maximum values shall be rounded to one decimal place and displayed to the specified number of digits. Percentages (%) and the upper and lower limits of their confidence intervals shall be rounded to the second decimal place and displayed to one decimal place.

- Significance Level and Confidence Coefficient

Unless otherwise specified, the significance level for hypothesis testing shall be two-sided 5 %. For interval estimation, unless otherwise stated, two-sided intervals shall be used with a confidence coefficient of 95 %. P-values shall be rounded to the fourth decimal place and displayed to three decimal places; however, if the unrounded p-value is less than 0.001, it shall be uniformly reported as "<0.001".

#### 9.1.1. Statistical Hypotheses

The primary objective is to evaluate the efficacy of sub-retinal administration of Montepilase (recombinant) for foveal hemorrhage in patients with SMH secondary to AMD or RAM.

For the primary endpoint—the change from baseline in CFT at Week 1—the 95 % confidence interval of the mean change shall be calculated, and a t-test shall be performed to assess statistical significance.

Accordingly, the null hypothesis to be tested for the primary endpoint is:

Null hypothesis: The mean change from baseline in CFT at Week 1 is 0.

Alternative hypothesis: The mean change from baseline in CFT at Week 1 is not 0.

#### 9.1.2. Adjustment for Multiplicity

The principal analysis for this trial is the t-test of the change from baseline in CFT at Week 1 performed on the Full Analysis Set (FAS). In principle, no adjustment for multiplicity will be applied to either the primary or secondary endpoints.

#### 9.1.3. Impact of Strategy for Intercurrent Events

Table 3-1 lists the interim events anticipated at the start of the trial. Considering the objectives of the trial, intercurrent events that are unlikely to represent clinical treatment failure, or for which the treatment strategy would be prioritized regardless of their occurrence, are handled

using a treatment policy strategy. Under the treatment policy strategy, all observed data regardless of the occurrence of intercurrent events will be included in the analysis.

Conversely, intercurrent events that are not aligned with the objectives of the trial are handled using a hypothetical strategy. Under the hypothetical strategy, the treatment effect is defined as if the intercurrent event had not occurred. To estimate this effect, data collected after the occurrence of the intercurrent event will be excluded from the analysis.

Furthermore, intercurrent events that are considered to represent clinical treatment failure are handled using a composite strategy. Under the composite strategy, the occurrence of the intercurrent event is incorporated into the endpoint definition. In this trial, a value representing no improvement will be assigned to such cases, and the analysis will be performed accordingly.

#### 9.1.4. Handling of Missing Data

The handling of missing data shall be described in detail in the Statistical Analysis Plan.

Except as specified in the Statistical Analysis Plan, missing values shall not be imputed as a general principle.

#### 9.2. Analysis Populations

For the purpose of analysis, the following analysis populations are defined.

| Analysis Population                     | Definition                                                                                                                                                                                           |
|-----------------------------------------|------------------------------------------------------------------------------------------------------------------------------------------------------------------------------------------------------|
| Informed Consent Population             | All subjects who provided informed consent.                                                                                                                                                          |
| Enrolled Population                     | All subjects who were formally enrolled.                                                                                                                                                             |
| Intervention Population                 | Subjects among the enrolled cohort who received the investigational drug. This group constitutes the primary safety analysis set.                                                                    |
| Intervention Discontinuation Population | Subjects among the enrolled cohort whose investigational drug administration was discontinued.                                                                                                       |
| Completion Population                   | Subjects from the trial-intervention population who completed the treatment period and observation period and attended a visit at week 12 (week 12 $\pm$ 7 days).                                    |
| Discontinuation Population              | Subjects from the trial-intervention population whose follow-up during the treatment period or observation period was discontinued and who did not attend a visit at week 12 (week 12 $\pm$ 7 days). |
| FAS (Full Analysis Set)                 | From the Intervention Cases, subjects meeting any of the following criteria are excluded. 
 
● No efficacy data exists after investigational drug
 
     |

|  |                                             |
|--|---------------------------------------------|
|  | administration.
● Serious GCP violation. |
|--|---------------------------------------------|

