| SMH secondary to AMD or RAM, using ophthalmic examination findings as indices.                         | 2) Presence or absence of a foveal hemorrhage measuring $\geq 1$ disc diameter at Week 4.
3) BCVA (logMAR equivalent) at Week 4.
4) Change in BCVA (logMAR equivalent) from baseline at Week 4.
5) Change in CFT from baseline at Week 12.
6) BCVA (logMAR equivalent) at Week 12.
7) Change in BCVA (logMAR equivalent) from baseline at Week 12. |
| Secondary (safety)                                                                                     |                                                                                                                                                                                                                                                                                                                                                                   |
| To evaluate the safety of subretinal administration of montepilase (recombinant) in patients with SMH. | Adverse events                                                                                                                                                                                                                                                                                                                                                    |

◆ Overview of the Overall Design

Intervention model: Single-arm

Control: Baseline control

Active comparator: None

Allocation method: None

Blinding: None

Target population type: Adult patients

Target population diagnosis: Submacular hemorrhage due to AMD or RAM

Target population age range: Minimum 18 years; no maximum

Distribution of study sites: Multicenter collaborative

Trial phase: Phase II

Committee: None

Duration per subject: 12-week observation period after enrollment

Planned sample size: 20 subjects

◆ Brief Summary of Trial Intervention and Observation

After obtaining written informed consent from the patient, those who satisfy all inclusion criteria and do not meet any exclusion criteria will be enrolled. Enrolled subjects will undergo pars plana vitrectomy, followed by subretinal administration of the investigational product diluted to 80,000 IU/mL, 0.1 mL (8,000 IU). Subsequently, a gas tamponade or silicone-oil exchange will be performed (Day 1). The primary endpoint will be assessed at 1 week post-

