#### 2.3.1. Risk Assessment

Adverse events that may occur with administration of monteplase (genetically engineered) include retinal toxicity (retinal morphological changes, etc.), increased sub-macular

hemorrhage, macular hole, vitreous hemorrhage, anterior chamber hemorrhage, endophthalmitis, elevated intra-ocular pressure, retinal detachment, corneal opacity, progression of cataract, etc. In addition to pharmacologic effects of the drug itself, events associated with vitreous surgery or intra-ocular tamponade are also encompassed.

To minimize these risks, the trial sites for this study shall be facilities that have prior experience with sub-retinal administration of tPA preparations, and patients at high risk will be excluded by the exclusion criteria.

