### 6. Study Interventions and Concomitant Therapies

Study interventions refer to all pre-specified investigational products, non-investigational study drugs, medical devices, and other interventions (e.g., surgical or behavioral interventions) that are used or performed on subjects during the conduct of the trial.

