| Intervention procedure | 
1) Perform local anesthesia or general anesthesia.
 
2) Conduct pars plana vitrectomy using a 3-port system with 23, 25 or 27-gauge instrumentation.
 
3) Phacoemulsification and intraocular lens implantation shall be performed at the discretion of the surgeon and according to the subject's preference.
 
4) Peeling of epiretinal membrane over the macula and internal limiting membrane is permitted.
 
5) Montepulse (recombinant) shall be administered with a sub-retinal injection needle into the sub-retinal hemorrhagic area located away from the fovea. Injection under the RPE and areas with RPE detachment shall be avoided to prevent RPE rupture. Multiple injection sites may be used as needed. During injection, intra-ocular pressure shall be monitored by palpation.
 
6) If retinal breaks are present, treat them with laser photocoagulation or cryotherapy.
 
7) Perform gas tamponade or silicone-oil exchange (the surgeon shall select either method based on the subject's severity, feasibility of positioning restrictions, etc.).
 
8) After montepulse (recombinant) administration, the subject shall remain in a supine or prone position for 20–60 minutes (including intra-operative time) according to the extent of hemorrhage. Thereafter, positioning restrictions shall be
 |

|                             |                                                                                                |
|-----------------------------|------------------------------------------------------------------------------------------------|
|                             | applied as directed by the surgeon, and the details shall be recorded in the case report form. |
| Related Intervention Labels | Monteplase (recombinant), vitrectomy, gas tamponade or silicone-oil exchange                   |

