##### 7.1. Discontinuation of Trial Intervention

If, prior to surgery, the principal investigator or sub-investigator determines that the subject's systemic condition has deteriorated such that sub-retinal administration of montepase (recombinant) cannot be performed, the trial intervention shall be discontinued.

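### The only named safety set requires receipt of monteplase, so a subject whose trial surgery is started but who is not injected drops out of the safety denominator, and no AEs are collected for that subject

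*Protocol*

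**What the plan says.** Protocol 9.2 defines the Intervention Population as "Subjects among the enrolled cohort who received the investigational drug. This group constitutes the primary safety analysis set". No other safety set is named. The FAS is built on the same group: "From the Intervention Cases, subjects meeting any of the following criteria are excluded". The one set that describes a stopped administration is the Intervention Discontinuation Population ("Subjects among the enrolled cohort whose investigational drug administration was discontinued"), and the protocol attaches no named analysis to it.

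Section 6 counts as study interventions also "other interventions (e.g., surgical or behavioral interventions) that are used or performed on subjects", and Table 6-1 lists vitrectomy and tamponade next to monteplase. The order is fixed. The synopsis in 1.1 says "Enrolled subjects will undergo pars plana vitrectomy, followed by subretinal administration of the investigational product". In Table 6-2, step 2 is "Conduct pars plana vitrectomy using a 3-port system", the injection is step 5 and the tamponade step 7. On risk, 2.3.1 states that "events associated with vitreous surgery or intra-ocular tamponade are also encompassed".

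Section 7.1 stops the intervention where "prior to surgery, the principal investigator or sub-investigator determines" that systemic deterioration rules out the injection. Tables 6-1 and 6-2 and section 6.6 deal with a difficult injection through a smaller dose or several injection sites. No passage deals with surgery that ends with no injection at all. Section 8.4.1 collects AEs and SAEs from the first administration onwards and records anything between consent and that moment as history or comorbidity.

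**The concern.** The regimen under test is an operation that includes a drug, and the operation comes first. The protocol accepts the surgical risks as risks of the trial, but admission to the safety set depends on reaching step 5. An intra-operative complication serious enough to prevent the injection takes the subject out of the denominator and the event out of the numerator. The exclusion can therefore depend on the outcome that the safety analysis is meant to measure. In a single-arm trial of 20 there is no comparator in which the same loss would show.

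**Working it through.** **1. Where the subject falls.** Take an enrolled subject in whom vitrectomy is started and no monteplase is given.

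| Set in 9.2 | Basis | Contains the subject? |
|---|---|---|
| Informed Consent, Enrolled | consent, enrolment | yes |
| Intervention (safety set) | drug received | no |
| Intervention Discontinuation | drug administration discontinued | can be read as yes; no named analysis |
| Completion, Discontinuation | subsets of Intervention | no |
| FAS | subset of Intervention | no |

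**2. Whether the events are collected.** Under 8.4.1 the collection period opens at the first dose. Without a dose it never opens. The AE definition in 10.2.1 is likewise tied to use of the investigational product. Set membership and event collection fail together, so both must be changed.

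**3. The plan's own figure.** Section 9.9 gives 19 subjects, raised to 20 for 5% dropout. A two-sided one-sample t-test with effect size 0.7 and alpha 5% needs n = 19 (power 82.3%), and 19/0.95 = 20. The figure reproduces. It serves here only as the denominator.

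**4. Chance that the case arises.** The protocol gives no rate p of non-injection, so p is assumed. P(at least one in 20) = 1 − (1 − p)^20.
- p = 1%: 1 − 0.99^20 = 18%
- p = 2%: 1 − 0.98^20 = 33%

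**5. Effect on the reported rate.** Suppose one of 20 operated subjects is not injected and has a serious complication, and no one else has one. Intervals are exact (Clopper-Pearson). With zero events the upper limit is 1 − 0.025^(1/n).

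| Rules | Reported | 95% CI |
|---|---|---|
| Present text | 0/19 = 0% | 0 to 1 − 0.025^(1/19) = 17.6% |
| 9.2 changed, 8.4.1 not | 0/20 = 0% | 0 to 1 − 0.025^(1/20) = 16.8% |
| 9.2 and 8.4.1 both changed | 1/20 = 5.0% | 1 − 0.975^(1/20) = 0.1% to 24.9% |

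The middle row shows that changing the set alone makes matters slightly worse: the subject enters the denominator without the event.

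**The case against.** A safety set of drug recipients is conventional. It matches the safety objective, which concerns sub-retinal administration of monteplase, and Table 6-1 classes vitrectomy as adjunctive surgery. Calling the set primary leaves room for a second one, and the SAP is not at hand. Partial doses count as received, so only zero-dose cases are affected, and 2.3.1 restricts the trial to sites with experience of the technique. The intervals in the table also overlap almost wholly. All of this limits the size of the point. It does not remove it, because the protocol fixes the set and the AE start itself, and an SAP that follows them inherits both.

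A reader might infer more than the documents support:

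- *That the FAS is equally wrong because the mean CFT change is conditional on technical success.* The treatment condition in the primary estimand is sub-retinal administration of monteplase, so an FAS of recipients follows from the chosen question. The effect would also be small. One eye with no change moves the planned mean from −120 to −120 × 19/20 = −114 µm, against a standard error of 170/√20 = 38 µm. Power at effect size 0.7 is 84.4%, 82.3% and 79.9% with 20, 19 and 18 subjects.
- *That the subject lies outside every analysis.* The Enrolled and Intervention Discontinuation Populations exist, and what the SAP does with them is unknown.
- *That the subject has no follow-up rule.* Section 7.2 allows discontinuation on safety or feasibility grounds at any time. It asks for discontinuation assessments unless no trial intervention has taken place, and for follow-up to 28 days if an adverse event is the cause. Examination data may therefore exist, but they do not enter the named safety set.
- *That such cases are likely.* Rates of 5% or 10% would give 64% or 88%, but the documents offer nothing to support them. At 1-2% the likelier outcome is no such subject at all (82% and 67%).

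**Conclusion.** The gap holds for safety. An operated but uninjected subject is outside the only named safety set, and that subject's events are never collected as AEs, although the protocol treats the surgery as a study intervention and its complications as trial risks. The surgical complication rate can therefore be understated, by one event in 20 (5 percentage points) for each such subject with a complication. This rests on two assumptions: a non-injection rate that the protocol does not give (18-33% chance of at least one case at 1-2%), and a complication as the reason for not injecting, which is an illustration and not protocol text. The primary efficacy analysis and the sample size are unaffected. The change is worth making before results are known, but the point does not threaten the main conclusion.

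**What to change.** - **9.2:** define the safety set as all enrolled subjects in whom the study surgery was started. Tabulate AEs for that set and for the injected subset, so that the drug-focused view is kept.
- **8.4.1:** start AE and SAE collection at the start of the study surgery, and check that the AE definition in 10.2.1 allows for this. Without this step the change to 9.2 captures nothing.
- **Reporting:** give the number of operated but uninjected subjects with the reasons.
- **Leave unchanged:** the FAS and the primary analysis stay on drug recipients, in line with the estimand.

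The cost is wording in two or three sections and one extra table. The safety figures may come out slightly less favourable.

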| Withdrawal of consent / loss to follow-up                                       |                                                                                                                 | Withdrawal of consent for reasons that have a major impact on the evaluation items (e.g., serious adverse events) | Composite variable             | Composite variable             | Composite variable              | Composite variable                               | Composite variable             | Composite variable | Composite variable              | Composite variable                                                        |
|                                                                                 |                                                                                                                 | Withdrawal of consent or loss to follow-up for reasons other than those described above                           | Virtual                        | Virtual                        | Virtual                         | Virtual                                          | Virtual                        | Virtual            | Virtual                         | Virtual                                                                   |
| Implementation of rescue therapy                                                | Photodynamic therapy                                                                                            | Treatment of underlying disease                                                                                   | Treatment policy               | Treatment policy               | Treatment policy                | Treatment policy                                 | Treatment policy               | Treatment policy   | Treatment policy                | Treatment policy                                                          |

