##### 7.2. Subject Discontinuation/Withdrawal

The trial for a subject shall be discontinued if any of the following applies:

- 1) The subject withdraws consent (the detailed reason for withdrawal shall be recorded in the case report form).
- 2) The subject is found to be ineligible after enrollment.
- 3) Based on a comprehensive safety assessment, including the occurrence of adverse events, the principal investigator or sub-investigator judges that continuation of the trial is infeasible (the detailed reason for infeasibility shall be recorded in the case report form).
- 4) The subject dies.
- 5) After trial initiation it becomes evident that, due to the subject's circumstances, required subsequent examinations or observations cannot be performed.
- 6) The subject meets the definition of loss to follow-up as defined in Section 7.3.
- 7) Any other situation in which the principal investigator or sub-investigator judges continuation of the trial to be infeasible (the detailed reason for trial discontinuation shall be recorded in the case report form).

At the time of discontinuation, appropriate medical care shall be provided based on the physician's judgment. To the extent feasible, the observations and examinations specified in the protocol for trial discontinuation shall be performed to evaluate safety. If the trial is discontinued because of an adverse event, the event shall be classified according to Section 10.2.3 (outcome categories 1, 4, 5) and follow-up of the adverse event shall be conducted up to 28 days after discontinuation. If follow-up cannot be performed, the reason shall be documented in the case report form. No discontinuation assessments shall be performed

for discontinuations that occur prior to any trial intervention.

A subject may withdraw from the trial at any time, for any reason or without providing a reason, upon the subject's own request, and no disadvantage shall result. Even if a subject withdraws consent, data collected prior to withdrawal shall, in principle, be included in the analysis set.

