#### 9.3.2. Primary Analysis Method

For CFT, the 95 % confidence interval of the mean change from baseline at week 1 will be calculated, and a significance test will be performed using a t-test.

Intercurrent events shall be handled as follows.

For vitreous re-surgery for ocular-complication treatment, sub-Tenon injection of triamcinolone acetonide, rescue therapy with photodynamic therapy or VEGF inhibitors, and the administration of prohibited concomitant therapy for other diseases such as defibrotide sodium or tPA preparations (including monteplase) (adopting a treatment policy strategy approach), all observed values of the primary endpoint shall be used in the analysis. For withdrawal of consent or loss to follow-up not due to serious adverse events, intravitreal gas injection as rescue therapy, and the administration of prohibited tPA preparations (including monteplase) as additional treatment for sub-macular hemorrhage (adopting a hypothetical strategy approach), data collected after the occurrence of the intercurrent event shall be excluded from the analysis in order to evaluate the treatment effect without these influences. For vitreous re-surgery due to re-bleeding, withdrawal of consent due to serious adverse events, and hematoma-removal surgery using prohibited concomitant therapy (adopting a composite strategy), the change value of 0 shall be imputed as the worst value for the primary endpoint in cases where the intercurrent event occurred, and these cases shall be analyzed accordingly.

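### The FAS exclusion for absent post-dose efficacy data has no exception for serious-adverse-event withdrawals, which the composite rule scores as failures with change 0

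*Protocol*

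**What the plan says.** The protocol fixes two rules that meet in the primary analysis.

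- **Who is analysed.** Section 9.1.2 states that the principal t-test is "performed on the Full Analysis Set (FAS"). Section 9.2 builds the FAS from subjects who received the drug and removes those for whom "No efficacy data exists after investigational drug" administration. No exception is given.
- **What value is used.** Table 3-1 (section 3) gives the composite strategy to "Withdrawal of consent for reasons that have a major impact on the evaluation items (e.g., serious adverse events"), for the primary endpoint and every secondary efficacy endpoint. Section 9.3.2 repeats this for "withdrawal of consent due to serious adverse events" and says that "the change value of 0 shall be imputed as the worst value for the primary endpoint in cases where the intercurrent event occurred".
- **Why that value.** Section 9.1.3 explains that "intercurrent events that are considered to represent clinical treatment failure are handled using a composite strategy", and that the event becomes part of the endpoint definition.
- **What happens at discontinuation.** Section 7.2 says: "To the extent feasible, the observations and examinations specified in the protocol for trial discontinuation shall be performed to evaluate safety". It also says that "data collected prior to withdrawal shall, in principle, be included in the analysis set".

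**The concern.** Under a composite strategy the outcome is known as soon as the event occurs. A subject who withdraws because of a serious adverse event has a change of 0 by definition, with or without an OCT. The FAS rule asks a different question, namely whether any efficacy data exist after dosing. For a subject who withdraws in the first days the answer may be no, and that subject is then absent from the set on which the value 0 was to be used.

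The case is possible. Section 2.3.1 lists endophthalmitis, retinal detachment and vitreous hemorrhage among the events that may occur. The schedule in section 1.3 has no OCT, fundus photography or acuity test on Days 2 to 4.

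At stake is the estimate in a single-arm trial. A failure that counts as 0 leaves the mean, and the reported reduction in CFT becomes larger than the one the estimand describes.

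**Working it through.** **1. The plan's own figure.** Section 9.9 assumes an effect size of 0.7 (mean change -120 µm, SD 170 µm), two-sided 5% and 80% power. A one-sample t-test with the noncentral t distribution gives n = 19 (power 0.823), and 19 / 0.95 = 20. Both stated numbers reproduce, so the sample size is not in question.

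**2. Who is lost.** This depends on what counts as efficacy data.

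- *Endpoint data only* (OCT, photography, acuity). The earliest such value is the Week 1 CFT. A subject who withdraws for a serious adverse event before then is excluded, unless a discontinuation examination is done. That examination is on the schedule, but section 7.2 requires it only where feasible. The retention of data collected before withdrawal does not help, because this subject has only baseline endpoint data.
- *Everything under section 8.2* (Efficacy Assessment Procedures). That section also contains intraocular pressure, slit-lamp and fundus examination, which the schedule places on Days 2, 3 and 4. Almost every dosed subject then has efficacy data, stays in the FAS and receives 0.

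**3. How many.** The protocol gives no number of early serious-adverse-event withdrawals, so k is an assumption. The planned dropout for all reasons is 5% of 20 = 1. The plausible range is therefore k = 0 (no effect) to k = 1.

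**4. Effect on the mean.** Take 20 dosed subjects, of whom 20 - k have mean change -120 µm and SD 170 µm.

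- Excluded, as section 9.2 reads: mean = -120 µm.
- Scored 0, as section 9.3.2 reads: mean = -120 × (20 - k) / 20. With k = 1 this is -120 × 19 / 20 = -114 µm.
- Overstatement: 20 / 19 - 1 = 5.3%.

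**5. Effect on the test, k = 1.** The SD of the 20 values, one of them 0, is the square root of [(18 × 170² + 19 × 120² - 20 × 114²) / 19] = the square root of (533,880 / 19) = 167.6 µm.

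| | Excluded | Scored 0 |
|---|---|---|
| n | 19 | 20 |
| Mean (µm) | -120 | -114 |
| SD (µm) | 170 | 167.6 |
| 95% CI (µm) | -201.9 to -38.1 | -192.5 to -35.5 |
| t | -3.08 | -3.04 |
| p | 0.0065 | 0.0067 |
| Power (simulated) | 0.828 | 0.828 |

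The shift of 6 µm is about 0.16 of a standard error (170 / √20 = 38.0 µm; 6 / 38.0 = 0.16).

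**The case against.** The best defence is that the group is very small. The protocol's own heading for section 8.2 makes the Day 2 to 4 examinations efficacy assessments, and they fall within the hospital stay. OCT, photography and acuity are scheduled at discontinuation with a window of +7 days. To be lost, a subject must withdraw for a serious adverse event within days of dosing, miss the discontinuation examination, and have the Day 2 to 4 findings not counted. Even then the estimate moves by 0.16 of a standard error. All of this stands, and it limits the point. It does not remove it, because neither the meaning of efficacy data nor the order of the two rules is stated.

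A reader might infer four stronger things that the protocol does not support.

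- *That the two rules flatly contradict each other.* One selects subjects and the other assigns values, so they can be run in sequence. What is wrong is that the sequence, as written, can discard a subject whose outcome is already defined.
- *That subjects re-operated for re-bleeding are lost too.* Re-operation does not end follow-up. These subjects normally have later data and are mostly unaffected.
- *That the definition stays open until results are known.* Section 9 says that the statistical analysis plan is finalized before database lock. Individual results are visible earlier in an open-label trial, but the text does not leave the choice until after the analysis.
- *That the overstatement reaches 11% or 18%.* Those figures need two or three such subjects (-108 or -102 µm when scored 0). That is two or three times the planned dropout for all reasons, placed in one rare subtype.

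**Conclusion.** The point holds in a narrow form. As written, the FAS definition can remove a subject whom Table 3-1 and section 9.3.2 count as a treatment failure. Only a serious-adverse-event withdrawal with no qualifying post-dose data is affected. The direction favours the drug whenever the remaining subjects show a mean reduction.

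With one such subject among 20 and the planned mean, the size is 6 µm (-120 instead of -114 µm, about 5%). On the broad reading of efficacy data it is close to nil. Power and p-value are essentially unchanged, so the harm is to the estimate and its match with the estimand, not to the test. This is not detail left for the statistical analysis plan: the exclusion and the composite value are both fixed in the protocol.

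**What to change.** Add to section 9.2 that dosed subjects with a composite-strategy event remain in the FAS with the composite value, whether or not efficacy data exist after dosing, and that the exclusion for absent efficacy data applies only to subjects without such an event. For the affected subjects it then no longer matters how efficacy data is defined.

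The cost is one sentence. Sample size, visits and procedures do not change. The downside is that the estimated reduction in CFT may be slightly less favourable.
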